### Equality and diversity

The study will be done across 16 regions throughout the UK and will include schools across the range of socioeconomic strata. School types reflect the variety of educational institutions across the UK as detailed in the study setting. Previous diversity information collected as part of UKMenCar4 across the same study network demonstrated that participants were reflective of their communities according to national census data.^20^ Inclusion of whole schools, rather than targeting individuals, will encourage equal participation of diverse populations.

### Sample handling and laboratory processes

Collected OPS will be placed immediately into STGG broth (skim milk, tryptone, glucose, glycerine; EO Labs, Bonnybridge, UK), maintained at 2°C–8°C until frozen at −80°C, within 4 hours of collection (figure 4). Site laboratories will thaw and plate the OPS sample on selective GC-VCAT Agar (vancomycin, colistin amphotericin B, trimethoprim; Thermo Fisher Scientific, Basingstoke, UK) at 37°C in 5% CO_2_ for up to 48 hours. Putative *Neisseria* spp. (oxidase positive, Gram-negative diplococci) will be subcultured on to Columbia Horse Blood Agar, then stored in a bead-based cryovial (Technical Service Consultants, Lancashire, UK) at −80°C.

**Figure 4 F4:**
[figure not shown]
Laboratory analysis plan. CC clonal complex; cgMLST, core genome MLST; GC-VCAT, vancomycin, colistin, amphotericin B, trimethoprim; MLST, multilocus sequence typing; rMLST, ribosomal MLST; STGG; skim milk, tryptone, glucose, glycerine.

The Public Health England Meningococcal Reference Unit (Manchester) will serogroup putative *Neisseria* spp. isolates using an in-house dot-blot ELISA using National Institute for Biological Standards and Control monoclonal antibodies against capsular polysaccharide serogroups B, C, W and Y.^26^ DNA will be extracted using a bead-based MagMAX DNA Multi-Sample Ultra Kit (Thermo Fisher Scientific, Massachusetts, USA). Total DNA extracts will be normalised prior to whole genome sequencing on the Illumina NovaSeq6000 platform (Oxford Genomic Centre, Wellcome Trust Centre for Human Genetics, University of Oxford).

Genomes will be assembled using an in-house assembly pipeline (Department of Zoology, University of Oxford) which incorporates Velvet and VelvetOptimiser.^27 28^ Assembled draft genome sequences will then be submitted to the open-access online database http://pubMLST.org/neisseria, with isolate providence data and FASTQ files uploaded to the European Nucleotide Archive and the Sequence Read Archive Databases. Automated locus annotation using the BIGSdb software platform will be used concurrently with manual curation for classification of isolates including species, clonal complex, lineage, genogroup and meningococcal typing schemes for multilocus sequence typing (MLST), ribosomal MLST, core genome MLST and vaccine antigen variants (eg, Bexsero Antigen Sequence Type).^29 30^ After study completion, genomes will be published open access on the pubMLST.org/neisseria database and OPSs, *Neisseria* spp. isolates and any products of culture on GC-VCAT media will be stored in an approved facility for further research.

### Potential benefits and harms

Participants will benefit from immunisation with a licensed ‘MenB’ vaccine which they would not otherwise receive in the UK immunisation schedule. Prior to enrolment, participants will receive information about 4CMenB and MenB-fHbp vaccination, according to the licensed product information. As a participant engagement exercise, all participants completing the final swabbing visit will be entered into a prize-draw for headphones. Participants will not receive payments.

### Safety reporting and study oversight

This study involves products used according to their licences. Safety monitoring will focus on detecting any serious adverse events (SAEs) and suspected unexpected serious adverse reactions (SUSARs). Specific SAE exemptions include traumatic injuries, hospital admissions for intoxication, deliberate self-harm or elective management of pre-existing conditions unless in response to a worsening of that condition since study enrolment. All SAEs will be reported to the chief investigator and to the sponsor, the University of Oxford Clinical Trials and Research Group. The Oxford University Hospitals National Health Service Foundation Trust/University of Oxford Trials Safety Group will review all new SAEs on a quarterly basis. SUSARs will be reported by the study chief investigator to the relevant competent authority and to the Research Ethics Committee. The lead site is the Oxford Vaccine Group, Department of Paediatrics, University of Oxford. The Scientific Advisory Board will provide input into study design, statistical analysis and will oversee safety reporting and study conduct in accordance with Good Clinical Practice. The Oxford Vaccine Group on behalf of the sponsor will act as the study monitor.

### Statistical methods

A baseline analysis will occur after wave 2 when the study reaches approximately 50% enrolment. This descriptive analysis of baseline carriage rates will assess the validity of the prospective sample size calculation. There will be no interim analysis of vaccine impact. The principal analysis will be conducted using a modified intention to treat approach, including all participants who have had two throat swabs. Participants will be analysed according to allocated group, regardless of vaccine receipt. Based on previous UK school-based meningococcal carriage studies, the design effect was assumed to be 1.5 in the sample size calculations but will be calculated on the actual data collected.^24 25^

For the primary objective and each of the secondary objectives, carriage rates will be expressed as a mean with two-sided 95% Clopper-Pearson CIs for each group at baseline and at 12 months. The carriage rates in the MenB-fHbp and 4CMenB groups will be compared separately to the Control Group. The OR with two-sided 95% CIs will be calculated using logistic regression via a generalised estimating equations model using an exchangeable working correlation structure. Model covariates will include age, gender, season of recruitment and baseline carriage status a priori. Additional risk factors found to affect carriage at baseline will also be included. Gender and smoking (smoking, home smoking and vaping) are known to affect both vaccine-induced immune responses and meningococcal carriage, and these interactions will be reported regardless of significance. The level of statistical significance will be 0.05. There will be no imputation of missing data for the principal analysis.

Sensitivity analyses will be done for the primary and each of the secondary objectives and will include: analyses without adjustment or inclusion of covariates for completeness and to confirm the results from the primary analyses; a per-protocol analysis of participants who received both vaccine doses in the 4CMenB and MenB-fHbp groups; adjustment for the month of the outcome measure rather than season of recruitment to further investigate the potential effect of seasonality and multivariable imputation for missing data. All variables that will be included in the analysis model will be included in the imputation model and will assume data are missing at random.

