## Methods

### Study design

The ‘Be on the TEAM’ (Teenagers Against Meningitis) Study is a pragmatic, partially randomised cluster controlled trial that will evaluate the carriage prevalence of pathogenic meningococci in adolescents vaccinated with either 4CMenB or MenB-fHbp, compared with a control group. Participants aged 16–19 years will be enrolled in 16 regions across the UK, with each region allocated to: (1) vaccination at 0 and 6 months with 4CMenB (‘4CMenB Group’); (2) vaccination at 0 and 6 months with MenB-fHbp (‘MenB-fHbp Group’) or (3) an unvaccinated Control Group who will be eligible for deferred vaccination with 4CMenB. Oropharyngeal swab samples (OPSs) will be taken at baseline and at 12 months.

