### Sample size

The sample size of 24 000 participants (8000 in each arm) is based on an estimated carriage rate 3.43% for genogroup B, C, W, Y or X in the Control Group at the 12-month swab. When assuming a retention rate of 80% and a design effect of 1.5, this sample size will provide 80% power to detect a 30% reduction of these genogroups combined, at a significance level of 0.05.

This anticipated carriage rate is based on results from the UKMenCar4 Study, which determined a carriage prevalence of 1.65% for genogroup B meningococcus, 2.3% for hyperinvasive meningococci and a combined prevalence of 4.2% for genogroup B, C, W, Y and X meningococci.^19^ The figure of 3.43% accounts for a potential 50% reduction in carriage of capsular groups W and Y due to the UK quadrivalent MenACWY vaccination programme; this figure is necessarily an estimate as there are limited data on the impact of the universal adolescent quadrivalent ACWY vaccine programme on carriage. A previous study in UK university students showed that immunisation with MenACWY-CRM reduced carriage of genogroup C, W or Y meningococci by 27.1% (95% CIs 6.9–42.9) and serogroup C, W or Y by 36.2% (95% CIs 15.6–51.7).^12^ A further UK university carriage cohort study suggested that the quadrivalent MenACWY vaccine exerts differential effects on capsular groups and did not prevent expansion of meningococci belonging to the hyperinvasive genogroup W clonal complex 11, although this was based on cross-sectional surveys rather than a longitudinal design.^21^

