### Randomisation, allocation and blinding

This is an open-label partially randomised study, with group allocation by study site. All schools within the geographical coverage area of each study site will be allocated to the same study arm, both for logistical reasons and because geographical allocation may increase the potential to detect any impact on herd protection. As a post-licensure study, blinded administration and/or placebo will not impact on the outcome of carriage prevalence and would introduce unnecessary cost and complexity to a trial of this scale. The allocation of initial sites was determined prior to the start of the study (figure 1). A capacity assessment stratified sites to either the control arm or immunisation sites depending on existing site expertise and the requirements to maintain equal numbers in each study arm. The immunisation sites were randomised to either the MenB-fHbp Group or the 4CMenB Group. Additional sites may be added during the study and will be pragmatically allocated to a study group to ensure balanced recruitment.

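### The Clopper-Pearson intervals planned for each group's carriage prevalence assume independent participants, so at the plan's design effect of 1.5 they have about 82% of the width they need

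*Protocol article*

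**What the plan says.** The Study design section of the protocol article calls the study a "pragmatic, partially randomised cluster controlled trial". Under Randomisation, allocation and blinding, "All schools within the geographical coverage area of each study site will be allocated to the same study arm". Participants are therefore grouped within schools, and schools within sites.

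The Sample size section allows for this grouping, "assuming a retention rate of 80% and a design effect of 1.5". Statistical methods returns to the point: "the design effect was assumed to be 1.5 in the sample size calculations but will be calculated on the actual data collected".

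The next paragraph of Statistical methods sets out two kinds of estimate for the primary and each secondary objective:

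- For single groups, "carriage rates will be expressed as a mean with two-sided 95% Clopper-Pearson CIs for each group at baseline and at 12 months".
- For each vaccine group against control, an odds ratio from "logistic regression via a generalised estimating equations model using an exchangeable working correlation structure".

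The second method provides for within-cluster correlation. The first is named without any modification, and no sentence links the calculated design effect to it.

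**The concern.** Clopper-Pearson limits come from inverting the binomial distribution, which treats every participant as independent. A design effect of 1.5 says that the variance of a group's carriage rate is 1.5 times the binomial variance. The article thus names an interval whose assumption conflicts with its own variance assumption. This goes beyond a detail left to a fuller document, because the method is stated.

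What is at stake is the accuracy of the published group prevalences. The primary objective is worded in terms of carriage prevalence in the groups, and the same interval is planned for every outcome at both time points. Followed as written, each nominal 95% interval would claim more precision than the design supports.

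**Working it through.** **Inputs, all from the protocol article**

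- Planned size: "The sample size of 24 000 participants (8000 in each arm").
- Control rate: "estimated carriage rate 3.43% for genogroup B, C, W, Y or X in the Control Group at the 12-month swab".
- A 30% reduction, so the vaccine-arm rate is 0.0343 × 0.70 = 0.02401.
- Retention 80%, so 8000 × 0.80 = 6400 swabbed per arm at 12 months.
- Design effect (DE) 1.5; power 80%; significance level 0.05, taken as two-sided.

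**Step 1: reproduce the plan's own figure**

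The usual two-proportion formula (pooled variance under the null, no continuity correction) for 3.43% against 2.401% gives 4196 per arm. Then 4196 × 1.5 = 6294, and 6294 / 0.80 = 7868. This is within 2% of the stated 8000. In the other direction, 8000 per arm gives an effective size of 6400 / 1.5 = 4267 and power of 80.7%. The sample size holds and already contains the design effect.

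**Step 2: width and coverage**

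The design effect multiplies the variance, so the standard error grows by √1.5 = 1.225.

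- Width of the plain interval relative to the required one: 1 / 1.225 = 0.816.
- Coverage of the plain interval: 2Φ(1.96 / 1.225) − 1 = 0.890.

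A beta-binomial simulation with the school-level correlation set to give a design effect of 1.5 (100,000 runs; 40 or 67 schools per arm, both assumed) gave coverage of 0.896 and 0.897.

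**Step 3: limits**

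With x = np, the lower limit is the 2.5% quantile of Beta(x, n − x + 1) and the upper limit is the 97.5% quantile of Beta(x + 1, n − x). The adjusted version uses n = 4267 in place of 6400.

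| Rate | Plain, n = 6400 | DE 1.5, n = 4267 | Widths (points) | Plain / adjusted |
|---|---|---|---|---|
| Control 3.43% | 3.00% to 3.91% | 2.90% to 4.02% | 0.908 and 1.116 | 0.81 |
| Vaccine 2.40% | 2.04% to 2.81% | 1.96% to 2.91% | 0.766 and 0.943 | 0.81 |

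**Step 4: range**

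The observed design effect is not in the document. If it were 2 or 3 (assumed values), the control limits would be 2.83% to 4.12% or 2.70% to 4.29%, and the plain interval would cover about 83% or 74%.

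**The case against.** Three points can be made for the plan.

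1. *The article never says that the intervals are unadjusted.* The sentence on calculating the design effect comes just before, and Clopper-Pearson on a reduced effective sample size is a recognised method, so the named interval could be meant that way. This is possible, but the text does not say it. The design-effect sentence contrasts the planning value with the observed one and assigns the observed one no use, while clustering is handled explicitly for the odds ratio. The ordinary reading is the standard interval, and one clause would settle the matter.

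2. *The intervals are descriptive.* This stands. No test, decision rule or power statement in the article uses them. The treatment comparison rests on the GEE model, and the sample size includes the design effect. This limits how serious the fault can be.

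3. *The practical harm is small.* This stands in part, because some stronger readings are tempting and fail:
   - A reader might infer that the narrow intervals could show groups as separate when the clustered comparison does not. In the table above the plain intervals are apart and the adjusted ones just touch. However, non-overlap of two 95% intervals is a stricter criterion than a test at 0.05. With 6400 per arm and 220 control carriers, the plain intervals just clear at 165 vaccine-arm carriers. The difference is 0.00859 and its pooled binomial standard error 0.00302, so z = 2.85. Dividing by √1.5 gives 2.32, and dividing by √2 gives 2.01. Both exceed 1.96. Lower counts behave alike (106 against 68, z = 2.37 at a design effect of 1.5; 60 against 32, z = 2.39). False separation would need a design effect above about 2, which the plan does not state.
   - A reader might infer that these limits will feed transmission modelling or the comparison before and after the MenACWY programme. The article says that the study informs both, but not that these particular limits are used.
   - A reader might infer much lower coverage by adding variation between regions to the school clustering. The article gives no between-region variation and does not say whether 1.5 already includes it, so no figure can be supported.

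**Conclusion.** The stated method is wrong for the design, at a minor to moderate level. At the plan's design effect, the group prevalence intervals have about 82% of the width they need and cover about 89% instead of 95%. The shortfall in width is the square root of the design effect, a factor of 1.22, not the factor of 1.5 that one might read straight from it. The GEE odds ratios and the sample size are not affected.

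The conclusion rests on two assumptions: that Clopper-Pearson is applied to the raw counts, as the text reads, and that the design effect is near 1.5. The article gives no separate design effect for the secondary outcomes, so the size of the fault may differ there.

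**What to change.** Add one sentence to Statistical methods: the confidence intervals for group carriage prevalence at baseline and 12 months will allow for clustering, with the cluster unit named. Either of two standard forms would serve:

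- Clopper-Pearson limits on the sample size divided by the observed design effect (the Korn-Graubard approach), with the design effect calculated for the outcome, group and time point concerned.
- Marginal prevalences from the GEE model with robust variance.

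If the first form was already intended, the sentence only needs to say so. No new data are needed, and the plan already commits to calculating the design effect. The only cost is wider intervals, by a factor of about 1.22 if the observed design effect is 1.5.

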Based on modelling estimates, an infant-only MenB immunisation programme may prevent 26.3% of all-age IMD in the first 5 years after introduction.^10^ If MenB vaccines could reduce meningococcal carriage by 30% and therefore disrupt transmission, a combined infant and adolescent immunisation programme could reduce all-age annual cases by 48.8% at 10 years and 59.7% at 20 years after introduction, enhancing impact and cost-effectiveness.^10^ The impact of 4CMenB immunisation on carriage has been studied in two randomised controlled trials (RCTs) to date. The ‘B Part of It’ cluster-RCT assessed the impact of immunisation with 4CMenB on carriage in 24 269 secondary school students in Australia.^11^ There was no impact on carriage of pathogenic genogroups A, B, C, W, Y or X at 12 months following immunisation. In the UK, 2954 university students were randomised to receive 4CMenB, MenACWY-CRM, or to an active control.^12^ This study showed no effect on the primary outcome of carriage prevalence 1 month after a two-dose schedule of 4CMenB. Using a composite end point of carriage at any timepoint 3–12 months following immunisation, administration of 4CMenB reduced carriage of any meningococcus by 18.2% (95% CI 3.4–30.8) and meningococcus groups B, C, W and Y combined by 26.6% (95% CI 10.5–39.9). This reduction was primarily due to a fall in carriage of meningococci of capsular groups C, W and Y, with a non-significant change in capsular group B meningococcal carriage. Only a minority of students at any institution received the vaccine, which reduced the potential impact of herd protection in the cohort. Studies assessing MenB-fHbp carriage impact are limited to observational reports of several small MenB outbreaks in US universities,^13^ where a number of interventions including mass-immunisation campaigns halted new cases, however these studies were not specifically designed or powered to show an impact of MenB-fHbp vaccine on carriage.

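### The outcome and power are stated as a fall in carriage prevalence, but the only adjusted between-group estimate is an odds ratio conditional on baseline carriage; a standardised prevalence ratio and difference should accompany it

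*Protocol article*

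**What the plan says.** All references are to the protocol article.

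- **Outcome.** The Abstract and Primary Objective define the primary outcome as carriage prevalence of genogroups B, C, W, Y or X at 12 months, each vaccine group against control.
- **Power.** Sample size starts from an "estimated carriage rate 3.43% for genogroup B, C, W, Y or X in the Control Group at the 12-month swab" and states "80% power to detect a 30% reduction of these genogroups combined, at a significance level of 0.05", with a design effect of 1.5 and 80% retention.
- **Modelling context.** Background and rationale describes a scenario: "If MenB vaccines could reduce meningococcal carriage by 30% and therefore disrupt transmission". The strengths and limitations list adds that the results will feed modelling of community-wide impact.
- **Adjusted analysis.** Statistical methods states: "The OR with two-sided 95% CIs will be calculated using logistic regression via a generalised estimating equations model". It continues: "Model covariates will include age, gender, season of recruitment and baseline carriage status a priori". Further risk factors found at baseline are to be added.
- **Other planned summaries.** The same section plans prevalence in each group at both swabs with Clopper-Pearson intervals, and sensitivity analyses without covariates. It names no prevalence ratio, prevalence difference or standardised estimate.
- **Allocation.** Randomisation, allocation and blinding says that a capacity assessment decided which sites were control and which were immunisation sites. Only the choice between the two vaccines was randomised.

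**The concern.** The question is a fall in prevalence, and the adjusted answer will be an odds ratio. With an outcome near 3% the two are usually treated as the same, and for the crude OR that is right. The adjusted OR is different because it conditions on baseline carriage. Among baseline carriers, carriage at 12 months may be common, and there the OR for a given risk ratio is well away from that ratio. A single OR pooled over carriers and non-carriers is pulled in the same direction. The GEE averages over clusters, not over covariates, so it does not undo this.

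At stake is the number that readers and modellers take away. The article expresses effects as percentage reductions: its own 30%, and the earlier university trial's 18.2%, 26.6%, 27.1% and 36.2%. No adjusted result on that scale is planned. Any gap between OR and ratio is systematic and does not shrink with sample size. A difference between the adjusted and unadjusted ORs could also be taken for confounding when it comes only from conditioning.

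**Working it through.** **1. The plan's own figure.** Inputs from Sample size: p1 = 0.0343, p2 = 0.70 × 0.0343 = 0.02401, 80% power, design effect 1.5, retention 80%. Alpha 0.05 is taken as two-sided, in line with the two-sided 95% intervals.

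n = [1.960·√(2p̄(1−p̄)) + 0.842·√(p1(1−p1) + p2(1−p2))]² / (p1−p2)², with p̄ = (p1+p2)/2, gives 4196 per arm. Then 4196 × 1.5 / 0.8 = 7868, or 8228 with continuity correction. The stated 8000 reproduces. The effective size is 8000 × 0.8 / 1.5 = 4267 per arm, which gives 80.7% power.

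**2. Odds-ratio scale without covariates.** OR = [0.02401/0.97599] / [0.0343/0.9657] = 0.693, against a prevalence ratio (PR) of 0.70. Read as a reduction this is 30.7% instead of 30%, a gap of 0.7 percentage points. A Wald test on this log OR has 80.2% power. OR = 1 and PR = 1 are the same null, so the power statement stands.

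**3. Adding baseline carriage.** Let b be the baseline prevalence, q1 the 12-month risk in control-group baseline carriers (persistence) and q0 the risk in control-group non-carriers. Overall control prevalence is fixed at 3.43%, so q0 = (0.0343 − b·q1)/(1 − b). The document gives no q1; 10% to 50% is assumed. With b = 3.43%, the share of control events that arise in baseline carriers equals q1.

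Both risks are multiplied by 0.70 in the vaccine arm, and a logistic model with arm and baseline status is fitted to the expected counts:

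| Assumed persistence q1 | q0 | Adjusted OR | 1 − OR | Standardised PR from the same fit |
|---|---|---|---|---|
| 10% | 0.0320 | 0.692 | 30.8% | 0.700 |
| 20% | 0.0284 | 0.686 | 31.4% | 0.700 |
| 35% | 0.0231 | 0.668 | 33.2% | 0.700 |
| 50% | 0.0178 | 0.633 | 36.7% | 0.700 |

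At 50% persistence, the OR among baseline carriers is (0.35/0.65)/(0.50/0.50) = 0.538, although their risk ratio is 0.70. That stratum pulls the pooled OR down. Averaging the fitted risks over the covariate distribution recovers 0.700 in every row.

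**4. Variations.**
- With b = 4.2% (the earlier UK survey's combined prevalence, used as an alternative assumption), the adjusted OR is 0.685 at 20% persistence and 0.615 at 50%.
- If the vaccine acts only on acquisition and overall prevalence still falls by 30%, the OR at b = 3.43% is 0.683 at 20% and 0.600 at 50%. At b = 4.2% and 50% it is 0.570.
- In reverse, a common conditional OR of 0.70 at b = 3.43% corresponds to a PR of 0.714 at 20%, 0.732 at 35% and 0.764 at 50%, that is, reductions of 28.6%, 26.8% and 23.6%.
- For an increase (PR 1.30 in both strata, b = 3.43%), the adjusted OR is 1.327 at 20% and 1.454 at 50%. The shift is away from 1 in both directions.

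**5. Set against sampling error.** At the effective size, SE(log OR) = √[1/(4267·p1(1−p1)) + 1/(4267·p2(1−p2))] = 0.131. The 95% interval around 0.693 is about 0.54 to 0.89.

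**The case against.** The strongest reply is that an OR reported as an OR overstates nothing. A logistic GEE is a legitimate, prespecified choice. Nowhere does the article say that 1 − OR will be read as a reduction, or that the OR is the modelling input. Further effect measures may be in the analysis plan, which is not shown. Unadjusted analyses are planned for every objective, and group prevalences will be published, so a reader can form a crude ratio. The size of the gap depends on a persistence that the document does not give; at 10% it is under one point, and even at 50% it is small beside the interval of 0.54 to 0.89.

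Much of this stands, and it rules out several stronger readings that a reader might infer:
- *That the trial misses or flatters a 30% policy threshold.* In Sample size the 30% is the effect for power, and in Background and rationale it is a modelling assumption. Neither is a success criterion.
- *That the OR is biased in the vaccines' favour.* Conditioning moves it away from 1 in either direction; a rise in carriage would be exaggerated too.
- *That the power or the test is wrong.* The null is the same, and 8000 per arm reproduces.
- *That a conditional OR is the only effect estimate planned.* The unadjusted analysis also gives one, and it is close to the prevalence ratio.
- *That ORs will be misread across the secondary endpoints.* No such comparison is planned.

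The crude figures still do not fill the gap. Control sites were chosen by capacity, not at random, so a crude ratio carries no protection against regional differences in carriage. Clopper-Pearson intervals treat participants as independent, although the same section assumes a design effect of 1.5. The unadjusted OR is also not a clean check on the adjusted one: in the table's setting they would differ (0.693 against 0.633 at 50% persistence) with no confounding at all.

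**Conclusion.** The point holds as a mismatch between the scale of the question and the scale of the adjusted answer. It is not an error in the sample size or the test. Read as a reduction, 1 − OR would exceed a true 30% fall by about 1 point at 10–20% persistence, 3 points at 35% and 7 points at 50%, assuming 3.43% prevalence at both swabs and the same risk ratio in carriers and non-carriers. The direction, away from no effect, was the same in every scenario computed. The size rests on an assumed persistence, and a material gap needs roughly 35% or more. The practical consequence is that no planned estimate is at once adjusted, cluster-corrected and on the prevalence scale. This is a modest point, worth making because the remedy is cheap.

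**What to change.** Keep the adjusted OR. Beside it, for each vaccine against control, report the covariate-standardised 12-month prevalence ratio and prevalence difference with cluster-corrected 95% intervals. Both come from the planned GEE logistic model by marginal standardisation: predict each participant's risk under each allocation, average, then take the ratio and the difference. A log-link Poisson GEE with robust variance is an alternative for the ratio. State that any comparison with the 30% reduction, and any input to modelling, uses these estimates and not 1 − OR. State also that adjusted and unadjusted ORs can differ without confounding.

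The cost is a sentence or two in the analysis plan and a few lines of code; no new data are needed. The intervals need a delta-method or cluster-bootstrap step that respects the same clustering as the OR. The headline reduction may be slightly smaller than 1 − OR would suggest.

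### The primary GEE does not name region, the unit of allocation, as its independent unit; with about 10-11 regions per contrast, default sandwich intervals would be too narrow

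*Protocol article*

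**What the plan says.** Under Study design, participants "will be enrolled in 16 regions across the UK, with each region allocated to" one of three groups. Randomisation, allocation and blinding adds: "All schools within the geographical coverage area of each study site will be allocated to the same study arm". The Discussion contrasts this regional allocation with the school-level cluster randomisation of the Australian trial. The number of regions is not closed: "Additional sites may be added during the study and will be pragmatically allocated to a study group to ensure balanced recruitment". The split by arm is in Figure 1, which is not shown.

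Under Statistical methods, each vaccine group is compared separately with control. "The OR with two-sided 95% CIs will be calculated using logistic regression", specifically "logistic regression via a generalised estimating equations model using an exchangeable working correlation structure". The a priori covariates are age, gender, season of recruitment and baseline carriage. Of the effects of gender and smoking the section says that "these interactions will be reported regardless of significance". It also states: "The level of statistical significance will be 0.05". It does not name the cluster, the variance estimator or the reference distribution. The one allowance for clustering, here and under Sample size, is a design effect of 1.5 taken from earlier school-based carriage studies.

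**The concern.** Arm is constant within a region, so the evidence on each vaccine effect comes from differences between regions. Thousands of pupils or many schools do not replace regions as the independent units. GEE inference with a sandwich variance is justified when there are many independent clusters, and here there are about 10 or 11 per contrast.

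The plan can be carried out in two natural ways. Clustering on region respects the allocation, but the uncorrected sandwich is too small with so few clusters. Clustering on school, which is where the design effect comes from, gives many clusters but treats schools in one region as independent. The article's own list of strengths and limitations refers to known variation in carriage across sites. It says that the scale of the study will compensate, but more pupils per region do not reduce variation between regions.

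At stake are the width of the 95% intervals and the true error rate of both primary comparisons of carriage prevalence.

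**Working it through.** **1. The plan's own figure.** Inputs from Sample size: 8000 per arm, 80% retention, design effect 1.5, control carriage 3.43%, 30% reduction (to 2.401%), two-sided 0.05. The effective size is 8000 × 0.8 / 1.5 = 4267 per arm. A pooled two-proportion z-test then has power 0.807. The required size is 4196 × 1.5 / 0.8 = 7868, against 8000. The stated 80% reproduces, but only with the school-based design effect and normal critical values.

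**2. Regions per contrast.** 16 / 3 = 5.33, so a balanced split gives 5 or 6 per arm and 10 or 11 per contrast. This is an inference.

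**3. Region as cluster, uncorrected sandwich, normal reference.** With K equal-sized regions per arm, the uncorrected variance is (K−1)/K times the unbiased one, and the properly scaled statistic follows approximately t on (regions − 2) degrees of freedom. True type I error ≈ P(|t| > 1.96 × √((K−1)/K)).
- 5 v 5: 1.96 × √(4/5) = 1.753; P(|t₈| > 1.753) = 0.118.
- 5 v 6 (average K = 5.5): 1.96 × √(4.5/5.5) = 1.773; P(|t₉| > 1.773) = 0.110.

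The between-region variance cancels from this ratio, so no ICC is needed.

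**4. Simulation under no vaccine effect.** 4000 trials per setting; 5 v 5, 5 v 6 and 6 v 5 regions; 12 schools of 100 or 8 schools of 150 analysed pupils per region; school-level design effect held at 1.5. The share of clustering variance placed at region level is assumed. The model contains arm only. Rejection rates at nominal 0.05:

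| Regional share | Region cluster, z | School cluster, z | Region, Kauermann-Carroll, t | Region, Mancl-DeRouen, t |
|---|---|---|---|---|
| 0% | 0.103-0.126 | 0.054-0.063 | 0.048-0.063 | 0.030-0.042 |
| 10% | 0.102-0.116 | 0.080-0.104 | 0.044-0.056 | 0.030-0.037 |
| 25% | 0.102-0.121 | 0.127-0.170 | 0.046-0.058 | 0.032-0.040 |
| 50% | 0.109-0.122 | 0.188-0.260 | 0.046-0.061 | 0.030-0.041 |

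The Monte Carlo standard error is about 0.005 at a rate of 0.11 and 0.003 at 0.05. A run of 20 000 trials (5 v 5, no regional variance) gave 0.118, 0.057, 0.052 and 0.034 in the same column order.

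**5. More sites.** At 8 v 8 regions with a 10% regional share, the rates were 0.088 (region, z) and 0.100 (school, z). Kauermann-Carroll with t gave 0.053.

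**6. Does 1.5 cover the region level?** Analysed pupils per region: 24 000 × 0.8 / 16 = 1200. A design effect of 1.5 at that level implies ICC = 0.5 / 1199 = 0.00042. The between-region coefficient of variation is then √(0.00042 × 0.9657 / 0.0343) ≈ 0.11. A coefficient of 0.20 (assumed) gives ICC = 0.04 × 0.0343 / 0.9657 = 0.00142 and a design effect of 1 + 1199 × 0.00142 = 2.7.

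**7. Power after correction.** Simulated at 5 v 5 with 6000 analysed per arm, for the 30% reduction: 0.68 (Kauermann-Carroll) or 0.59 (Mancl-DeRouen) with no regional variance; 0.56 or 0.47 with a 10% share. The plan expects 6400 analysed per arm. At 6000 the formula in step 1 gives 0.78, so the smaller number explains only a little of the fall.

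**The case against.** The strongest reply is that the quoted sentence contains nothing false. It names no variance estimator, reference distribution or cluster, a corrected sandwich with a t reference is compatible with it, and such detail is often left to an analysis plan that is not shown here. That stands as far as it goes: the article does not commit to an uncorrected interval, and its silence is not itself an error. What remains is that the article fixes a method whose default form needs many clusters, in a design with few, and draws its only clustering allowance from schools and not from the allocated unit.

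A reader might also infer more than the text supports:
- **That school clustering is invalid in every case.** It is near nominal if there is no regional variance. No regional ICC is given, and adjustment for baseline carriage and other covariates could absorb part of the variance. The simulations are unadjusted.
- **That the error is at least double the nominal 5% in general.** This holds for the uncorrected region-clustered test at about 10-11 regions. It does not hold for school clustering when the regional share is small.
- **That the model has more parameters than regions, so the covariance cannot be estimated.** This would need the smoking terms and every interaction in the primary model. The stated terms are an intercept, two arms and four covariates: seven, against 16 regions. Further risk factors enter only if they affect baseline carriage, and the interactions are to be reported, not necessarily fitted in the primary model.
- **That false claims of herd protection would follow.** The primary endpoint is carriage prevalence by arm, and that is what the error rate concerns.

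**Conclusion.** The concern holds in conditional form. With the usual uncorrected sandwich and a normal reference, region clustering gives a true two-sided type I error of about 11-12% for each primary contrast. This assumes a roughly balanced split of the 16 regions and near-equal region sizes, but nothing about regional variance. School clustering gives about 5.5-6% if regional variance is zero, about 8-10% if 10% of the clustering variance is regional, and 13-26% across the assumed shares of 25-50%. The article's own remark on variation between sites makes zero a poor planning value. Adding a few sites would lessen the region-clustered error but not remove it. Covariate adjustment may reduce the school-clustered error but does not cure the shortage of clusters. Because both primary comparisons are affected, the analysis should be specified before outcome data are examined.

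**What to change.** - State that region, the unit of allocation, is the GEE cluster in both primary comparisons.
- Use a small-sample-corrected sandwich variance (Kauermann-Carroll or Mancl-DeRouen) with a t reference on regions minus cluster-level parameters: 10 − 2 = 8 or 11 − 2 = 9 for a two-arm contrast under a balanced split.
- Confirm with a region-level summary analysis, for example a t-test on the regional log-odds of carriage.
- Report the gender and smoking interactions from separate models, so that the primary odds ratio is a main-effect estimate and not the effect in a reference category.
- Restate power on this basis.

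The change is one of analysis wording and uses available methods. Its price is precision. At 5 v 5 the log-odds interval widens, relative to the uncorrected one, by 2.306/1.96 × √(5/4) = 1.32 (Kauermann-Carroll) or 2.306/1.96 × 5/4 = 1.47 (Mancl-DeRouen). Power falls below the stated 80%. Mancl-DeRouen is somewhat conservative here (0.030-0.042), while Kauermann-Carroll is closer to nominal (0.044-0.063), so one should be chosen in advance.
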